### Study Design

A 2-arm randomized controlled trial is being conducted to test the efficacy of the minimally guided web-based program Selfapy for GAD. The web-based course is defined as minimally guided as it is completed independently by the participant. However, as part of the patient safety concept, a psychologist monitors the participant’s progress to support the patient and respond to adverse events, such as suicidality. The participants can ask a psychologist questions about the program via an integrated messaging function. Figure 1 shows the schematic study design for patients in the intervention group and control group. After a structured diagnostic interview (DIPS-OA [26]) to clarify the inclusion and exclusion criteria, eligible patients will receive the first questionnaire and subsequently will be randomly assigned to the intervention group or control group. Patients in the intervention group will be able to use Selfapy immediately after randomization, while the control group will only have access to Selfapy after a waiting period of 12 weeks. Interim and final evaluations will occur 6 weeks (T2) and 12 weeks (T3) after the entry survey.

Subjects in the intervention group will have free access to the 12-week internet-based self-help treatment. Participants are advised to spend at least 15 to 20 minutes per day on the program. If no module is finished over 4 weeks, this will be counted as a dropout for an additional sensitivity analysis. Patients in the control group will not receive any treatment or support from the researchers during the first 12 weeks after the initial survey. However, they are free to seek any other assistance they desire, including pharmacological and psychological treatments. All concurrent therapies will be repeat-measured using self-reports.

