### Hypotheses

The main objective of this trial is to determine the efficacy of the 12-week Selfapy course for patients with GAD compared to a wait-list control group. Additional outcome data will be collected at 6 weeks. However, our confirmatory hypotheses, which will evaluate a positive health care effect, will focus on the 12-week outcomes. The following 2 hypotheses refer to our primary outcomes:

GAD symptomatology (measured with the GAD-7 [27]) will significantly decrease with the use of the Selfapy course for GAD after 12 weeks compared to a wait-list control group.Perceived quality of life (measured with the WHO-5 [28]) will significantly increase after 12 weeks of the Selfapy course for GAD compared to a wait-list control group.

The following secondary outcomes will only be analyzed if the hypotheses for the primary outcomes are confirmed. They will also be tested using Bonferroni-Holm adjustment:

Difficulties in daily life (measured with the WSAS [30]) will significantly decrease after using the Selfapy course for GAD after 12 weeks compared to a wait-list control group.Using the Selfapy course for GAD will lead to significantly better recovery of working ability (measured with the iPCQ [32]) after 12 weeks compared to a wait-list control group.Health literacy (measured with the MHLS [34]) will significantly improve with the use of the Selfapy course for GAD after 12 weeks compared to a wait-list control group.The extent of therapy-related efforts and burdens of patients and their relatives (measured with the CSSRI [35]) will be significantly reduced after using the Selfapy course for GAD compared to a wait-list control group after 12 weeks.

Our exploratory hypotheses do not address the target symptoms and are therefore not adjusted for α accumulation:

Worry symptoms (measured with the PSWQ [36]) will significantly decrease with the use of the Selfapy course for GAD after 12 weeks compared to a wait-list control group.Self-rated anxiety symptoms (measured with the BAI [39]) will significantly decrease with the use of the Selfapy course for GAD after 12 weeks compared to a wait-list control group.Self-rated depressive symptoms (measured with the PHQ-9 [41]) will significantly decrease with the use of the Selfapy course for GAD after 12 weeks compared to a wait-list control group.The Selfapy course for GAD will not lead to any side effects compared to a wait-list control group after 12 weeks (measured with the NEQ [42]).

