### Randomization and Blinding

Subjects meeting the inclusion criteria will be randomly assigned to 1 of 2 groups and will receive either (1) immediate access to the minimally-guided Selfapy GAD course (the intervention group) or (2) access to the Selfapy GAD course after a waiting period of 12 weeks (the control group).

Randomization takes place after the participant has finished the entry questionnaire, which is conducted by a member of the psychology department who is not involved in the project, using a computer-assisted procedure. Random assignment is done only if participants fulfill the inclusion criteria for the study. Until this time, which group the person will be assigned to if included is unknown (allocation sequence concealment). Participants will be assigned to 1 of the 2 groups in a nonstratified 1:1 ratio. Subjects will be informed of the outcome of the random assignment via email. Participants are told that the waiting time will randomly vary between 0 and 12 weeks. Thus, patients in the control group will not know that the sample is divided into 2 groups. One group will start the intervention immediately while the other group will wait 12 weeks before receiving access to the therapy. The diagnostic interviewers will be blind to the group membership of the participants. After completing data collection, statistical analysis of the outcomes will also be performed in a blinded manner.

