### Statistical Analyses

For the psychometric outcome analyses, all patients who were randomly assigned to the 2 conditions and completed the initial survey (T1) will be included in an intention-to-treat (ITT) analysis. All available data will be used for this purpose. Missing values in the data will be replaced by multiple imputations (multivariate imputation by chained equations with n=5 imputations) based on the control arm, using the variables “age” and “gender” as predictors in addition to the measurement-repeated stress indicators. In addition, last-observation-carried-forward, baseline-observation-carried- forward, reference-based-multiple imputation (jump-to-reference approach [49]), and completer sensitivity analyses will be performed.

The confirmatory analysis of the primary outcomes consists of calculating a mixed model with 2 measurement time points and a general correlation structure [47]. A random effect for the subjects is calculated (random intercept) and 3 fixed effects (group assignment, time, and the interaction of the 2 predictors). The 2 measurement time points are nested within subjects. The primary outcomes will be evaluated using a Bonferroni-Holm correction for α error inflation. Secondary confirmatory outcomes will only be analyzed if the results of the primary analysis confirm the hypotheses, and the same mixed model with a random intercept for the subject will be applied. Again, a Bonferroni-Holm correction will be used.

Independent 2-tailed *t* tests and chi-squared tests will be used to estimate differences between groups in pretreatment sample characteristics. In addition to the ITT sample, a “per-protocol” sample sensitivity analysis is defined for exploratory analyses, including all patients in the intervention group who completed at least 4 of the modules.

There are different approaches to calculating effect sizes for mixed modeling data in the literature [50]. Hedges [50] and Westfall et al [51] propose an effect size based on the Cohen *d*, which is also used for power analysis [47]:

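### Baseline significance tests are uninformative here, and prespecified adjustment for T1 covariates already collected would give the primary models a small, nearly free gain in precision

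*Protocol article*

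**What the plan says.** Four places in the protocol article bear on this.

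- **Baseline comparison (Statistical Analyses).** Two-tailed t tests and "chi-squared tests will be used to estimate differences between groups in pretreatment sample characteristics". The article attaches no decision to the results.
- **Primary model (Statistical Analyses).** The confirmatory analysis consists of "calculating a mixed model with 2 measurement time points and a general correlation structure", with a subject random intercept and "3 fixed effects (group assignment, time, and the interaction of the 2 predictors"). No baseline covariate is listed. Age and gender are named only as predictors in the multiple imputation. The Hypotheses section says the confirmatory hypotheses "will focus on the 12-week outcomes", so the two time points are read here as T1 and T3. The effect-size paragraph identifies the group-by-time interaction as the treatment effect.
- **Allocation (Randomization and Blinding).** "Participants will be assigned to 1 of the 2 groups in a nonstratified 1:1 ratio". The assignment is not known until the entry questionnaire has been completed.
- **Available information (Study Design; Table 1).** Other psychological and pharmacological treatment is permitted, and "All concurrent therapies will be repeat-measured using self-reports". PHQ-9, service use (CSSRI) and a demographic questionnaire are all listed at T1.

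**The concern.** When allocation is random and concealed, the null hypothesis of a baseline test is known to be true. A small p-value then flags a chance event, and a large one does not show that an imbalance is harmless. Whether an imbalance matters depends on its size and on how strongly the variable predicts the outcome, and a significance test measures neither.

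The tool that does deal with imbalance is prespecified covariate adjustment, and the model as listed does not use it. The trial admits patients with other primary diagnoses and with other treatment under way, and it does not stratify. Depression and current treatment at T1 could therefore plausibly predict change and could differ between arms by chance. At stake are some precision in both primary comparisons and the reading of the result if such an imbalance occurs.

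**Working it through.** **Inputs from the article (Power and Sample Size):** d = 0.45, directed hypothesis, alpha 0.025, power 0.80, 78 per arm, 156 in total. **Not in the article, so assumed:** the T1-T3 correlation, the strength of the covariates and the share of patients in other treatment at T1.

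**1. The plan's own figure.** Power = Phi(0.45 x sqrt(78/2) - 1.960) = Phi(2.810 - 1.960) = Phi(0.850) = 0.802. The stated 156 is reproduced. This takes 0.45 in units of the SD of change, which equals the raw SD if the T1-T3 correlation is 0.5.

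**2. False flags from baseline tests.** The article does not say how many variables are tested. With k independent tests at 0.05, the chance of at least one significant result is 1 - 0.95^k: 37% for 9, 43% for 11 (nine scales plus age and gender), 54% for 15. The scales are probably correlated, so these figures are a guide only.

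**3. Which part of an imbalance reaches the estimate.** With complete data at two time points, the interaction is the between-arm difference in mean change. A covariate effect that is equal at T1 and T3 cancels. Only the difference between its T3 and T1 effects remains. For PHQ-9, with assumed correlations of 0.6 with the outcome at T1 and 0.4 at T3, that is 0.4 - 0.6 = -0.20 SD per SD of imbalance. Simulation of 20,000 trials gave the same slope of about -0.20.

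**4. Size of that part.** The standardised arm difference in any baseline variable has SE sqrt(2/78) = 0.160, so its 95% limit is 1.96 x 0.160 = 0.314. Three ways of sizing the shift at that limit:
- PHQ-9 as in step 3: 0.314 x 0.20 = 0.06 SD.
- 40% in other treatment at T1 and a 0.4 SD effect on change (both assumed): SD of the arm difference in share = sqrt(2 x 0.4 x 0.6/78) = 0.078, and 1.96 x 0.078 x 0.4 = 0.06 SD.
- Covariates explaining 5% or 10% of the variance of change: 0.314 x sqrt(0.05) = 0.07 SD and 0.314 x sqrt(0.10) = 0.10 SD.

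Against 0.45, a shift of 0.06 to 0.10 is 14 to 22%. It can go in either direction.

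**5. Validity of the planned analysis.** In the same simulation (T1-T3 correlation 0.5), the planned interaction averaged -0.001 under no effect and 0.450 under d = 0.45. One-sided type I error was 0.026, and the SD of the estimate was 0.160.

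**6. Gain from adjustment.** Power = Phi(0.45/sqrt(1 - R2) x sqrt(39) - 1.960):

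| R2 of change (assumed) | Power | Equivalent total N, 156/(1 - R2) |
|---|---|---|
| 0 | 0.80 | 156 |
| 0.05 | 0.82 | 164 |
| 0.10 | 0.84 | 173 |

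This is a gain of 2 to 4 points, equal to 8 to 17 extra patients.

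**7. Form of the adjustment.** On one simulated data set of 156, covariate main effects alone left the interaction and its SE unchanged (-0.57022, SE 0.17148). Adding covariate-by-time terms reduced the SE to 0.16871. The time interactions are therefore what matters.

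**The case against.** The strongest reply is that an unadjusted analysis of an unstratified trial is valid, and that its standard error already allows for chance imbalance. That is correct, and it rules out several stronger readings that a reader might infer:

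- **That imbalance biases the primary estimates or passes into them in full.** It does neither. The interaction is unbiased over repeated randomisation, and covariate effects that are constant over time cancel. Each outcome's own T1 value is already in the model as a response.
- **That the baseline tests decide comparability or the choice of model.** The article states no such rule. The fixed effects are prespecified, and the analysis is blinded to arm.
- **That the T1 data are unused.** PHQ-9 and CSSRI are outcomes in their own right, and age and gender enter the imputation. They are only absent as covariates in the primary model.
- **That the sample size is wrong on this ground.** It is reproduced without any covariate.

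Three further points stand. The sizes rest on assumptions, and excluding severe depressive episodes narrows the range of PHQ-9. Adjusting for the outcome's own baseline would gain more: in the simulation power rose from 0.80 to 0.89, and adding PHQ-9 after that gave 0.90. The remedy also takes more than one model line. Covariates would shrink the random-intercept variance used in the effect-size denominator, the imputation model may not contain all the covariates, and a yes/no treatment variable has to be defined from the CSSRI.

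These points limit the size of the concern and shape the fix. They do not make the baseline tests informative, and they do not make adjustment costly.

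**Conclusion.** The point holds as a cheap improvement. The planned baseline tests are uninformative, and the primary model leaves out baseline covariates that are already collected. The planned estimate is unbiased with correct type I error, so the primary analysis is not invalid.

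The cost has two parts. One is a modest loss of precision, about 2 to 4 points of power if the covariates explain 5 to 10% of the variance of change. The other is exposure of this single trial to the change-related part of a chance imbalance, roughly 0.06 to 0.10 SD at the 95% extreme. Both sizes depend on assumed covariate strength, which the article does not give. If the outcome's own baseline is also adjusted for, the additional power from these covariates is smaller.

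**What to change.** - Replace the baseline t and chi-squared tests with means, SDs and percentages by arm.
- Prespecify a short list of T1 covariates for the GAD-7 and WHO-5 models: PHQ-9, concurrent psychotherapy or medication (yes/no, with its derivation from the CSSRI defined), age and gender. Enter each with its interaction with time. Use T1 treatment status only, because treatment begun after randomisation is not a baseline variable.
- Include the same variables in the imputation model.
- Take the effect-size denominator from the unadjusted model, so that d stays on the planned scale.
- Report the unadjusted model as a sensitivity analysis.

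The article reports that all participants had finished by May 2023. If the data have already been analysed, keep the planned model as primary and report the adjusted one as a labelled sensitivity analysis. The baseline tests can still be left out of the report.

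The cost is some wording, a coding rule and slightly more analysis work, with no new data. With complete data, four covariates take the degrees of freedom for the comparison of change from 156 - 2 = 154 to 156 - 6 = 150.

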While most of the literature focuses on guided forms of iCBT with therapeutic support, minimally guided, self-directed iCBT programs also show large effect sizes in the treatment of GAD (eg, Cohen *d*=2.43 [21]). Dear et al [22] found no significant differences between guided and unguided iCBT in terms of symptom reduction, completion rates, and satisfaction in the treatment of GAD. Moreover, first evidence suggests that characteristics of the guidance, such as the frequency of supportive monitoring [23], type of reminder (eg, phone, email), and the experience or training of the support person [24], do not have a significant influence on GAD symptom reduction. Nevertheless, it is important to take steps to promote adherence and minimize the typically high dropout rates of web-based, particularly self-directed, interventions [25] (eg, motivational content).

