### Additional Outcomes

The Penn State Worry Questionnaire (PSWQ [36]) is used to assess worry as an accompanying syndrome of GAD; it consists of 16 items rated on a 5-point Likert scale. The PSWQ shows internal consistencies approximately in the range between α=.84 [37] and α=.86 [38] in GAD patients.

The Beck Anxiety Inventory (BAI [39]) is used to assess the severity of anxiety in adults and adolescents. It consists of 21 descriptive statements rated on a 4-point scale. The internal consistency of the BAI is α=.90 in clinical samples. The German version was validated by Margraf and Ehlers [40].

The Patient Health Questionnaire-9 (PHQ-9 [41]) is used to assess the presence and severity of depressive disorders. The PHQ-9 consists of 9 items rated on a 4-point Likert scale and has an internal consistency of α=.89.

To capture possible negative effects of the intervention, the Negative Effects Questionnaire (NEQ [42]) is used, which consists of 32 items rated on a 4-point Likert scale. The NEQ has an internal consistency of α=.95.

The adherence of the intervention group is recorded via the log files of the web-based platform Selfapy. The number of modules that have been worked on is recorded.

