## Discussion

This study tests the efficacy of a minimally guided web-based intervention (Selfapy) for the treatment of GAD in routine clinical care. The study has several strengths. First, the study was designed to strike a balance between a high degree of internal validity (eg, randomization, a standardized diagnostic procedure), allowing us to attribute observed group differences to the intervention with sufficient certainty and a high external validity (eg, allowing participants to use additional health care services) to evaluate the effects in an ecologically valid context. In particular, we did not prepare artificial measures to increase adherence to gain a representative impression of routine care patient adherence. Second, to the best of our knowledge, this study is one of the most highly powered studies on iCBT for GAD [13]. Third, we will investigate outcomes beyond symptom reduction, such as functioning and health care use. Limitations of this study include the lack of an active control group instead of a wait-list control group, even though this design allows only limited conclusions regarding the specificity of the effects found. We chose this design in an attempt to assess the incremental effect of Selfapy for GAD patients compared to the current situation in the German health care system. Patients who want to undergo outpatient psychotherapy in Germany have to wait for an average of 20 weeks to start treatment [19]. One of the main advantages of an internet intervention like the one investigated in this study is its availability. If implemented in routine clinical care, patients can make use of these interventions without delay and can expect results comparable to traditional face-to-face therapy [14]. One could argue that the waiting period in the control group (12 weeks) is too short, given the average waiting time in the health care system of 20 weeks. Still, we decided to restrict the waiting time in the control group to 12 weeks for several reasons. First, for ethical reasons, we wanted to limit the waiting time as much as possible. Withholding a likely helpful intervention should only be done as long as necessary. Again, we want to highlight that patients in the control group, as well as those in the intervention group, were allowed to seek additional treatment and help if they thought it necessary. No patients were asked to refrain from any other mental health services. Second, 12 weeks is the time the intervention takes when completed on the recommended schedule. Therefore, fixing the control group to the same measurement schedule as the intervention allows us to evaluate the effects of having access to Selfapy for GAD compared to not having access to this intervention. Another limitation lies in the use of deception in telling the patients that the intervention will start some time between 0 and 12 weeks later. This is done to attenuate dissatisfaction with being in the control group. However, patients in the control group may still feel dissatisfied and unlucky when they have to wait what they think is the maximum amount of time for the intervention. Also, we do not assess the frequency of personality disorders, which may be reasonable because GAD is associated with higher rates of personality disorders [53]. Further limitations include the lack of follow-up measurement, the lack of a power calculation for the secondary outcomes, and the lack of a mindfulness measure despite the intervention including a mindfulness-based approach.

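### The per-protocol set filters only the intervention arm on module use, so its contrast with controls is not randomised and cannot serve as a robustness check on the ITT result

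*Protocol article*

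**What the plan says.** All places are in the protocol article.

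- **Main analysis** (Statistical Analyses): "all patients who were randomly assigned to the 2 conditions and completed the initial survey (T1) will be included in an intention-to-treat (ITT) analysis". The confirmatory test is the group-by-time effect in a mixed model with two time points.
- **Per-protocol set** (Statistical Analyses): in addition to ITT, a per-protocol sample is set up as an exploratory sensitivity analysis, "including all patients in the intervention group who completed at least 4 of the modules". No criterion is given for controls.
- **Access** (Study Design): "the control group will only have access to Selfapy after a waiting period of 12 weeks".
- **Source of module data** (Additional Outcomes): "The adherence of the intervention group is recorded via the log files of the web-based platform Selfapy".
- **Expected adherence**: no completion rate is given. The Background speaks of a need to "minimize the typically high dropout rates of web-based, particularly self-directed, interventions", and the Discussion says that "we did not prepare artificial measures to increase adherence".

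**The concern.** The per-protocol rule selects on something that happens after randomisation and can be observed in one arm only. The controls who would have completed 4 modules, had they been given access, cannot be identified, so the control arm stays whole while the intervention arm is reduced to its more engaged members. The two groups then differ by treatment and by whatever makes people persist with a self-help programme.

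The planned model does not repair this. The group-by-time term removes a difference in baseline level between engaged users and controls. It does not remove a difference in the change that they would have shown anyway.

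What is at stake is interpretation. A set labelled a sensitivity analysis invites the reader to take agreement with ITT as corroboration, or to take a larger estimate as the effect in people who use the programme properly. This contrast can support neither. With adherence expected to be limited and not actively raised, the filter may remove a sizeable part of the arm.

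**Working it through.** **The plan's own figure.** Power and Sample Size gives d = 0.45, a directed hypothesis, α = .025, power 0.80 and 1:1 allocation. Per arm, n = 2 × (1.960 + 0.842)² / 0.45² = 77.5, rounded up to 78, so 156 in total. This matches the protocol. No figure is given for the per-protocol analysis.

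**Inputs for the check**

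- 78 per arm and a one-sided test at 0.025, from Power and Sample Size.
- f, the share of the intervention arm completing at least 4 modules: not in the documents, assumed.
- r, the correlation of engagement with a favourable *baseline-adjusted* outcome: not in the documents, assumed. It must be baseline-adjusted because the group-by-time model already removes level differences.

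**Formulas, with a true effect of zero.** If the most engaged share f is kept and all 78 controls are retained:

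- spurious d = r × φ(c) / f, with c = Φ⁻¹(1 − f);
- SE = √(1/(78f) + 1/78);
- rejection rate = 1 − Φ(1.96 − d/SE).

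**Numbers for f = 0.5.** c = 0, φ(c)/f = 0.399/0.5 = 0.798, and SE = √(1/39 + 1/78) = 0.196.

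- r = 0.2: d = 0.16; rejection = 1 − Φ(1.96 − 0.81) = 13%.
- r = 0.3: d = 0.24; rejection = 1 − Φ(1.96 − 1.22) = 23%.

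**Simulation** (zero effect, 78 per arm, 20,000 runs per setting, one-sided t test at 0.025):

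| Share kept f | r | Spurious d | Rejection |
|---|---|---|---|
| 0.5 | −0.2 | −0.16 | 0.3% |
| 0.5 | 0 | 0.00 | 2.6% |
| 0.5 | 0.1 | 0.08 | 6.0% |
| 0.5 | 0.2 | 0.16 | 12.1% |
| 0.5 | 0.3 | 0.24 | 22.4% |
| 0.4 | 0.3 | 0.29 | 27.3% |
| 0.7 | 0.1 | 0.05 | 4.7% |
| 0.7 | 0.3 | 0.15 | 13.3% |
| 0.9 | 0.3 | 0.06 | 5.3% |

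Formula and simulation agree to within about one percentage point. For scale, 0.16/0.45 = 0.36 and 0.24/0.45 = 0.53, so at f = 0.5 and r = 0.2 to 0.3 the artefact is about a third to a half of the planning effect. That comparison is rough, because the spurious d is in SD units of the baseline-adjusted outcome.

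**The case against.** **The set is exploratory.** The article presents it as an addition to ITT and nowhere says that it supports the efficacy claim. This stands. The hypotheses, the α level and N = 156 do not depend on it, and a reader who inferred that the confirmatory result is compromised would be wrong. What remains is the sensitivity label, which suggests a check that this contrast cannot provide.

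**Size and direction are not known.** A reader might infer that the analysis would show benefit without any effect, or that its bias must favour the programme. The documents do not support this. They give neither f nor r, there is no bias at r = 0, and the sign reverses if people who recover early stop using the programme. Even at f = 0.4 and r = 0.3, most null trials would not reject. Only *could* is justified. Still, a contrast whose bias has unknown sign and size cannot confirm another analysis.

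**The dropout rule.** Study Design adds: "If no module is finished over 4 weeks, this will be counted as a dropout for an additional sensitivity analysis". A reader might infer a second one-arm filter. The article defines the dropout but does not say whether such patients are removed, censored or imputed. If they were imputed by the jump-to-reference method listed under Statistical Analyses, they would be drawn towards the control arm, and the result would be conservative. How they are handled is the kind of detail that an article leaves to the full protocol, so no fault is claimed here.

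**All controls is itself an inference.** The article does not state who the comparators are. It is the only practical reading, because without controls there is no between-group comparison.

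**The remedy can overstate too.** Dividing the ITT effect by the share completing at least 4 modules assumes no effect in those completing 1 to 3. With a 50% share, an ITT d of 0.45 would become 0.45/0.5 = 0.90. The ratio also gives essentially the same test as ITT, so it adds an estimate for users and no independent evidence. Both points stand and shape the fix.

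**Conclusion.** The point holds for the per-protocol set, as a minor one. The rule filters one randomised arm on behaviour that the other arm cannot show, so the resulting contrast is not randomised, and the group-by-time model does not restore comparability in expected change. It cannot be used to judge how robust the ITT result is.

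The possible size rests wholly on assumed values. Over completion of 40% to 70% and r of 0.1 to 0.3, the formula gives a spurious d of 0.05 to 0.29 and false-positive rates of about 5% to 28%, against a nominal 2.5%. The artefact shrinks as completion rises, is absent at r = 0 and runs against the programme when r is negative. The ITT analysis is unaffected.

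**What to change.** 1. Add a complier-average causal effect at T3 with random allocation as instrument, for example by two-stage least squares with the T1 score as covariate and module use from the log files. Controls have no access before T3, so non-compliance is one-sided. If the programme has no effect in anyone, this estimator targets zero, whatever the relation between engagement and prognosis.
2. Make completion of at least one module the main exposure. The exclusion restriction, that allocation has no effect in those counted as unexposed, is most plausible there.
3. Give the version with at least 4 modules second, flagged as likely to overstate the effect if users of 1 to 3 modules benefit.
4. If the filtered set is kept, report it as a non-randomised descriptive comparison that does not support the efficacy claim, and state which controls it uses.

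**Cost.** A few lines of code and no new data. The interval is wider: at an exposed share of 50%, in outcome SD units and taking the share as known, the standard error is about √(2/78)/0.5 = 0.32, against 0.20 for the filtered contrast. The exclusion restriction cannot be tested fully. Any analysis using module counts also shows the analyst which group code is the intervention, so it should follow completion of the blinded ITT analysis.
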